## Abstract

**Background:**

In 2023, U.S. Perinatal HIV Guidelines shifted from recommending exclusive formula feeding to endorsing shared decision-making for infant feeding among pregnant and postpartum persons with HIV (PPWH) on antiretroviral therapy (ART) with sustained viral suppression. While the risk of HIV transmission through breastfeeding is small (< 1%) with sustained viral suppression, adherence protocols are complex and clinical support infrastructure remains underdeveloped. Doula care has demonstrated benefits for breastfeeding initiation, maternal anxiety reduction, and postpartum follow-up, yet no studies have examined HIV-specialized doula programs supporting infant feeding choice among non-English speaking PPWH in North America.

**Objective:**

Using a patient-centered, community-informed framework, BRIDGES (BReast and Infant feeding Doulas to address Gaps in Education and Support) is an HIV Doula education and support program designed to improve maternal/child health outcomes and reduce perinatal transmission. The program aims to support heterogeneous infant feeding options through doula-mediated prenatal education, ART adherence support, lactation counseling, and postnatal care coordination.

**Methods:**

In collaboration with the Pediatric Community Advisory Board, South Florida Health Departments' Perinatal HIV Programs, and University of Miami (UM) Ob/Gyn, a doula-based intervention was developed for pregnant and postpartum women with HIV. The study employs a sequential mixed-methods design: Aim 1 builds the BRIDGES intervention through community engagement, embedding an Infant Feeding Choice Community Advisory Group; Aim 2 evaluates BRIDGES in a single-arm interventional study of 15 mother–baby dyads. Data collection includes sociodemographic, clinical, obstetrical, and psychosocial measures (HIV stigma, medical mistrust, resilience), along with individual and group interviews. The Consolidated Framework for Implementation Research (CFIR) guides evaluation of implementation determinants.

**Results:**

The BRIDGES intervention pairs each mother–infant dyad with an HIV-trained doula from enrollment during pregnancy through 12 weeks postpartum. The doula supplements clinic education with prenatal education on infant feeding options (breastfeeding, formula, banked donor milk), ART adherence support, lactation counseling, and guidance on clinical monitoring protocols specific to feeding choice. Clinical monitoring protocols differentiate between breastfeeding dyads (monthly maternal viral load, infant ARV prophylaxis until weaning, enhanced infant HIV testing) and formula-feeding dyads (standard of care).

**Significance:**

BRIDGES addresses a critical gap at the intersection of evolving HIV infant feeding guidelines and doula-supported perinatal care. This intervention was shaped by a collaborative effort that ensures its cultural relevance, linguistic inclusivity, and alignment with community needs, amplifying its potential impact on supporting infant feeding choice among PPWH. Findings may inform other U.S.-based HIV clinics providing pregnancy care services to PPWH.

**Clinical Trial Registration:**

Identifier: NCT07664423. https://clinicaltrials.gov/study/NCT07664423.

## Introduction

1

Each year, approximately 3,500–5,000 women with HIV give birth in the United States (1–3). Through universal prenatal HIV screening, combination antiretroviral therapy (ART), and until recently complete avoidance of breastfeeding, the perinatal HIV transmission rate declined from approximately 25% in the pre-ART era to 0.9% by 2019, achieving the national elimination goal of less than 1% (1, 3, 4). A 2025 systematic review and meta-analysis of approximately 80,000 mother–child pairs found zero observed perinatal transmissions among women who started ART before conception and maintained a viral load below 50 copies/mL through delivery (5). This success, however, came at a cost: the blanket recommendation against breastfeeding failed to account for the immunologic, nutritional, bonding, and cardiometabolic benefits of human milk for both mother and infant (6, 7), and disproportionately affected Black, Hispanic/Latino, and immigrant communities for whom breastfeeding carries deep cultural significance and for whom breastfeeding disparities are already pronounced. Breastfeeding initiation among Black infants (74.5%) lags substantially behind White (85.3%) and Hispanic (86.8%) infants nationally (8, 9).

In 2023, the U.S. DHHS Perinatal HIV Guidelines were updated to endorse shared decision-making for infant feeding among PPWH on ART with sustained viral suppression, acknowledging that the risk of postnatal HIV transmission through breastfeeding is very low, up to 1%, though not zero (6, 10, 11). The American Academy of Pediatrics (AAP) 2024 Clinical Report and the Infectious Diseases Society of America (IDSA) 2024 primary care guidance followed with concordant recommendations (7, 12). Yet standardized clinical infrastructure to deliver this new paradigm consistently across sites remains limited, even as some individual programs have developed local procedures to support shared decision-making. No data inform the optimal frequency of viral load monitoring during breastfeeding; no data exist on postnatal transmission risk with mixed feeding while on ART; infant ARV prophylaxis strategies vary from no prophylaxis to three-drug regimens through weaning with no consensus; and only an estimated 184–214 breastfeeding infants with perinatal HIV exposure have been described across observational studies in high-income settings, none designed to evaluate transmission (5, 10, 11). A 2025 meta-regression updating global vertical transmission probability estimates for the UNAIDS Spectrum-AIM model found that breastfeeding transmission probabilities were revised upward compared to prior default values, further underscoring the need for structured support and monitoring for breastfeeding PPWH (13).

Adherence protocols are complex: PPWH who breastfeed must maintain 100% ART adherence, undergo enhanced maternal and infant viral load monitoring, manage breastfeeding complications (mastitis, cracked nipples, infant thrush) that may warrant temporary interruption, and navigate weaning all while contending with HIV stigma, medical mistrust, and postpartum depression, which occurs more frequently among individuals with HIV (7, 10, 11). A survey of U.S. HIV specialty providers found that one-third were aware that patients breastfed after being advised not to do so, underscoring the urgent need for structured support (11).

Successful breastfeeding among PPWH depends not only on patient autonomy but also on access to accurate, evidence-based education and comprehensive clinical support. Challenges may be particularly pronounced among marginalized populations, which often face disproportionate barriers within the U.S. healthcare system. In a qualitative study of a predominantly multicultural population in South Florida, breastfeeding was viewed as an important cultural and familial practice, yet barriers caused mainly by misinformation prevented informed infant-feeding decisions (14). Among participants, 45% identified fear of HIV transmission through breastfeeding as a barrier, while 25% reported experiencing societal and cultural pressures related to infant-feeding practices (14). These concerns may influence infant-feeding decisions, impacting both evidence-based feeding practices and neonatal health. Given the multitude of intersectional factors influencing infant-feeding practices, additional support should be directed toward developing culturally responsive interventions that address the barriers faced by women living with HIV.

Doula care has demonstrated consistent benefits for breastfeeding initiation, maternal anxiety reduction, and postpartum follow-up. A 2026 systematic review of 21 clinical trials found doula care most consistently associated with improved breastfeeding initiation and reduced maternal anxiety (15), and a large retrospective cohort study (*N* = 17,831) demonstrated 20% higher exclusive breastfeeding rates with doula support, with effects consistent across race and insurance status (16). Doulas have been identified as a promising strategy to mitigate racial disparities in maternal-infant outcomes (17–19). Beyond improving clinical outcomes, doulas provide culturally appropriate care and informational support that may help address structural barriers. Research has shown that doula support is associated with a 25% reduction in cesarean deliveries and reduced rates of preterm birth among historically marginalized populations (20). A retrospective cohort study of deliveries recorded from January 2021 to December 2022 found that patients with doula care experienced more frequent vaginal birth after C-Section (VBACs), fewer preterm and early preterm deliveries, fewer indicated preterm deliveries, and higher rates of exclusive breastfeeding (18). In the postpartum period, individuals who delivered under doula care were also more likely to continue and engage with postnatal care within 6 weeks of delivery. Although that study did not specifically include PPWH, the findings align with the key components required for successful breastfeeding in this population, including sustained engagement in care, adherence to ART for both mother–infant dyads, maintenance of viral suppression, and consistent postpartum monitoring.

As infant-feeding recommendations increasingly emphasize shared decision-making, doulas may serve as valuable members of the perinatal care team by providing culturally competent care and supporting informed infant-feeding decisions. However, no published studies have evaluated HIV-specialized doula programs in the United States. The Kotawêw study in Canada is the sole published work examining doula care within the HIV care continuum, describing Indigenous doulas as providing peer mentorship, practical HIV education, stigma reduction, and structural advocacy (21). BRIDGES (BReast and Infant feeding Doulas to address Gaps in Education and Support) is the first U.S. HIV-specialized doula intervention supporting infant feeding choice. Conducted at the University of Miami (UM) Department of Obstetrics, Gynecology and Reproductive Sciences which has cared for more than 4,000 PPWH in South Florida, a region with among the highest rates of perinatal HIV in the nation (4, 22) this exploratory pilot study employs a sequential mixed-methods design and aims to: (1) build a patient-centered, community-informed HIV doula program that supports infant feeding choice while maintaining viral suppression, informed by an Infant Feeding Choice Community Advisory Group, with qualitative analysis of Advisory Group input guiding intervention development; (2) evaluate the feasibility and acceptability of BRIDGES in a single-arm interventional study of 15 mother–baby dyads with heterogeneous feeding intentions, including qualitative analysis of participant interviews; and (3) generate preliminary data to inform a future multi-site trial generalizable to U.S.-based HIV clinics providing pregnancy care to PPWH.

## Methods and analysis

2

### Development of study team to address community needs

2.1

A multidisciplinary team will inform the BRIDGES study, bringing together HIV clinicians, obstetricians, pediatricians, doulas, implementation scientists, and community members with lived experience of HIV, including women with HIV who have been pregnant or postpartum, to ensure that input on intervention design reflects the perspectives of the women the program is intended to serve. The collaborative was built upon the belief that to address community needs, interventions must be designed and developed not only for the community, but with the community. The study team includes the UM Women's HIV Clinic, the UM Center for AIDS Research (CFAR) Clinical Research Unit, and South Florida Health Departments' Perinatal HIV Programs.

Central to this approach is the establishment of an Infant Feeding Choice Community Advisory Group, embedded within the existing Pediatric Community Advisory Board. This Advisory Group (maximum 20 members) will be recruited from the Pediatric HIV Community Advisory Board and will include men and women ≥18 years old who have experience working with or are living with HIV, including women with HIV who have lived experience of infant feeding decision-making, and are able to communicate at the 6th grade level in English, Spanish, or Haitian Creole. The Advisory Group will also include several members with personal birthing and infant feeding experience, even if not living with HIV, as dual lived experience of HIV and infant feeding is considered especially valuable. The Advisory Group will meet twice initially to establish the board, then once every 6 weeks thereafter, with meetings lasting approximately one hour. Advisory board notes will be taken, de-identified, and analyzed qualitatively for research purposes. Advisory Group members will not receive financial compensation, consistent with their role as advisors rather than research participants. This structure ensures that the intervention is informed by the lived experiences of people with HIV and the expertise of perinatal HIV providers, consistent with best practices for community advisory boards in HIV research (10, 12).

### Theoretical frameworks

2.2

BRIDGES is grounded in two complementary frameworks. First, the Consolidated Framework for Implementation Research (CFIR) guides evaluation of implementation determinants across five domains: intervention characteristics, outer setting, inner setting, characteristics of individuals, and process (23, 24). CFIR has been successfully applied to evaluate prevention of vertical (perinatal) HIV transmission (PMTCT) programs (25), where it identified key constructs distinguishing high- and low-performing facilities, including networks and communication, available resources, external change agents, executing, and reflecting and evaluating. In the BRIDGES study, CFIR will serve as both a planning tool during intervention development (Aim 1) and a deductive coding framework during qualitative analysis (Aim 2).

Second, a patient-centered, shared decision-making model consistent with the 2023/2025 U.S. Perinatal Guidelines and the 2024 AAP Clinical Report anchors the intervention's clinical approach. This shared decision-making approach is consistent with current U.S. perinatal HIV infant-feeding guidelines (7, 11). This model emphasizes nonjudgmental counseling, exploration of motivations and barriers, and support for autonomous infant feeding decisions (7, 10, 11). The doula serves as the primary vehicle for operationalizing shared decision-making, providing sustained, culturally concordant support that bridges clinical recommendations and individual values, preferences, and feeding plans.

### Study design and setting

2.3

The development of this clinical trial, from the study design to the protocols, is an iterative process that will involve extensive feedback from the study team, Advisory Group, and clinical partners.

**Study design:** This is an exploratory, single-arm, mixed-methods interventional study employing a sequential design in which Aim 1 (community engagement and intervention development) informs the implementation of Aim 2 (interventional study). The protocol will be registered on ClinicalTrials.gov prior to enrollment.

**Study setting:** All study activities will take place at the UM Women's HIV Clinic and the UM CFAR Clinical Research Unit in Miami-Dade County, Florida. Study procedures may also be conducted via Zoom for Healthcare. South Florida represents an ideal setting: the region has among the highest rates of HIV transmission in the United States. An analysis of 4,337 singleton births with perinatal HIV exposure reported to the Florida Department of Health found a 1.6% perinatal transmission rate, with late maternal HIV diagnosis as the primary driver of missed prevention opportunities (22). The population is racially, ethnically, and linguistically diverse, with significant representation of communities disproportionately affected by HIV, including Black, Hispanic/Latina, and Haitian Creole-speaking populations.

### Participants

2.4

**Advisory Group members (Aim 1):** Men and women ≥18 years old who have experience working with or are living with HIV and are able to communicate at the 6th grade level in English, Spanish, or Haitian Creole. Maximum of 20 members.

**Patient participants (Aim 2):** Inclusion criteria are women ≥18 years old with a documented HIV diagnosis; currently pregnant or postpartum; residing in South Florida; and able to communicate at the 6th grade level in English, Spanish, or Haitian Creole. Exclusion criteria are persons not able to verbally consent in English, Spanish, or Haitian Creole. There is no maximum age. Target enrollment is *N* = 15 mother–baby dyads.

Women who are virologically suppressed throughout pregnancy may also enroll after delivery and receive the postnatal component of the intervention; enrollment timing (prenatal versus postnatal) will be recorded to account for differential exposure to intervention components.

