Clinical monitoring protocols are differentiated by feeding choice. For mothers who initiate breastfeeding: mothers will continue ART throughout breastfeeding, with the goal of maintaining HIV viral load < 50 copies/mL; infants will receive ARV prophylaxis until weaned off breast milk; maternal HIV viral load will be monitored monthly for up to 3 months or until the infant is weaned, consistent with the guideline recommendation of monitoring every 1–2 months; infant HIV nucleic acid testing will follow the schedule recommended by the AAP (at 14–21 days, 1–2 months, 4–6 months, every 2 months during lactation, and at 4–6 weeks and 3 and 6 months after weaning); breastfeeding will be temporarily interrupted or discontinued if maternal viral load becomes detectable, particularly if ≥200 copies/mL; and the doula will educate on and monitor for breastfeeding complications (mastitis, cracked/bleeding nipples, infant thrush) that may warrant temporary breastfeeding interruption (6, 7, 10, 11). For mothers who elect to formula feed: standard of care will be followed, with infant ARV prophylaxis for 4 weeks and viral load measured at birth, 2 weeks, and 4 weeks.

For mothers who breastfeed, expressed-milk pumping and pasteurization (including exclusive pumping) will be offered as a supported option during viral blips, mastitis, or other periods of increased transmission risk for those who prefer not to introduce formula. Infant antiretroviral prophylaxis will be provided for the duration of breastfeeding per site protocol, and banked donor milk (including use as a supplement to the mother's own milk) will be supported, with data collected on source and frequency of use. Specific infant ARV regimen and prophylaxis decisions will follow the treating clinical team's guidance and institutional protocol.

The clinical monitoring protocols follow guideline-based standard of care and are fixed; the doula-delivered intervention components (educational content, materials, and delivery approach) and recruitment procedures are co-developed and iteratively refined with the Advisory Group and clinical partners. The Advisory Group structure will be established within the existing Pediatric Community Advisory Board framework. Participants will be enrolled during pregnancy regardless of infant feeding intention, allowing the study to capture the full spectrum of infant feeding decisions and the doula's role in supporting each choice.

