### Outcomes

2.9

As an exploratory pilot/feasibility study, the primary outcomes are feasibility and acceptability.

Primary outcomes include recruitment and retention rates, intervention completion rate and doula visit attendance; participant-reported experiences and acceptability (qualitative interviews and, if adopted, a satisfaction survey); and ART adherence and maintenance of viral suppression. Clinical and psychosocial measures are framed as exploratory signal-detection outcomes to inform a future multi-site trial (Aim 3).

Secondary outcomes include infant feeding method chosen and duration; breastfeeding complications (mastitis, cracked nipples, infant thrush, low milk supply); infant HIV testing completion and results; postpartum visit attendance; and changes in psychosocial measures (HIV stigma, medical mistrust, resilience).

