### Data analysis

2.10

**Quantitative analysis:** Descriptive statistics will characterize the study sample and summarize clinical outcomes. Metrics will include recruitment rate, retention rate, doula visit attendance, and intervention completion, with confidence intervals reported around key feasibility proportions (e.g., retention). As a pilot, the sample size (*N* = 15) is based on feasibility and resource considerations rather than a formal power calculation. Within-participant change over the study period (e.g., maintenance of viral suppression across pregnancy and the postpartum period, breastfeeding duration for those who elect to breastfeed, and infant HIV testing completion) will be summarized descriptively. Because this is a single-arm pilot without a control group, no between-group effect estimation or controlled pre-post inference is implied.

**Qualitative analysis:** Audio-recorded interviews will be transcribed and analyzed using thematic analysis with password-protected, cloud-based qualitative data processing systems (Dedoose). Analysis will employ line-by-line coding, constant comparison, and axial coding to identify central themes. CFIR constructs will be used as a deductive coding framework to evaluate implementation determinants (23, 24), supplemented by inductive codes emerging from the data. If both individual and group interviews are retained for participants (pending the decision in Section 2.6), they will be analyzed as separate data sources rather than pooled.

**Mixed-methods integration:** Quantitative and qualitative findings will be integrated using a convergent design, with results triangulated to provide a comprehensive understanding of intervention acceptability and preliminary effectiveness. Qualitative data from both Aim 1 (Advisory Group) and Aim 2 (participant interviews) will be used to refine the BRIDGES intervention for future testing.

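### Post-delivery entrants meet the pregnancy part of the viral-suppression outcome by their entry condition, and section 2.10 does not separate them from prenatal entrants

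*Protocol article*

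**What the plan says.** All references are to the protocol article.

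- **Entry (2.4 Participants).** The inclusion list admits women "currently pregnant or postpartum; residing in South Florida" and sets no viral-load condition. A later paragraph adds: "Women who are virologically suppressed throughout pregnancy may also enroll after delivery and receive the postnatal component of the intervention". The same sentence continues: "enrollment timing (prenatal versus postnatal) will be recorded to account for differential exposure to intervention components".
- **Entry elsewhere.** Section 2.5 says "Participants will be enrolled during pregnancy regardless of infant feeding intention", and section 2.6 likewise places enrollment in pregnancy.
- **Outcome (2.9 Outcomes).** The primary outcomes include "ART adherence and maintenance of viral suppression". The same section frames clinical measures as exploratory signals for a later multi-site trial.
- **Analysis (2.10 Data analysis).** As an example of within-participant change to be described, the plan names "maintenance of viral suppression across pregnancy and the postpartum period". Entry route is not mentioned there, and neither is the timing flag.

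**The concern.** The late route selects women on part of an outcome that the study then reports. A woman who enters after delivery under that sentence cannot fail the pregnancy part: she was admitted because she had already met it, and BRIDGES had no contact with her during that time. A woman who enters in pregnancy can fail it.

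The timing flag is recorded for a different reason. Differential exposure means that late entrants received less of the program, which would suggest a weaker result for them. Selection on suppression suggests a stronger one. A reader told only about exposure could take good results in late entrants as a sign that the postnatal component alone is enough.

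What is at stake is how a suppression figure can be read. If it covers pregnancy and postpartum for all 15 women, it reflects the recruitment mix as well as the program, which makes it a poor signal to pass on to the future trial named in Aim 3.

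**Working it through.** There is no planned figure to reproduce. The sample size of 15 rests on feasibility and resources, and the article gives no expected suppression rate and no split of entry routes.

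**Inputs**
- N = 15 dyads (section 2.4).
- k = number of post-delivery entrants. Not stated and not capped, so assumed: 0, 5 or 10.
- s = proportion of prenatal entrants suppressed throughout pregnancy. Not stated, so assumed: 0.7, 0.9 or 1.0.
- q = proportion maintaining suppression postpartum, taken as equal in both groups. Not stated, so assumed: 0.9.
- Post-delivery entrants suppressed in pregnancy: 100%, by the entry sentence in section 2.4.

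**Pregnancy part alone.** Summary over all women = (k + (15 − k)s)/15. With s = 0.7:
- k = 0: 10.5/15 = 70%
- k = 5: (5 + 7)/15 = 80%
- k = 10: (10 + 3.5)/15 = 90%

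Each prenatal entrant replaced by a post-delivery entrant adds (1 − s)/15. That is 2.0 points at s = 0.7, 0.7 points at s = 0.9 and nothing at s = 1.0.

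**Pregnancy plus postpartum**, the period named in section 2.10. Summary = q(k + (15 − k)s)/15. With q = 0.9:

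| s | k = 0 | k = 5 | k = 10 |
|---|---|---|---|
| 0.7 | 63% | 72% | 81% |
| 0.9 | 81% | 84% | 87% |
| 1.0 | 90% | 90% | 90% |

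Postpartum performance is the same in every cell, so the movement along a row comes only from the recruitment mix.

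**Postpartum only.** Let a be the rate in prenatal entrants and b the rate in post-delivery entrants. Summary = ((15 − k)a + kb)/15.
- a = 0.80, b = 0.90: 80% at k = 0, 87% at k = 10
- a = b = 0.90: 90% at any k
- a = 0.95, b = 0.85: 95% at k = 0, 88% at k = 10

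So the upward drift is built into the pregnancy part. In the postpartum part it can go either way.

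**Split by entry route.** With s = 0.7 and q = 0.9, prenatal entrants show 0.7 × 0.9 = 63% over both periods and post-delivery entrants show 90% for postpartum only. Neither expected figure depends on k.

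**Scale.** The exact (Clopper-Pearson) 95% interval for 12/15 is 52% to 96%. For 7/10, the matching prenatal-only count at k = 5 and s = 0.7 for the pregnancy part, it is 35% to 93%.

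**The case against.** The strongest reply is that the article never plans one suppression proportion over all 15 women. Section 2.10 gives suppression as an example of something to be described, promises intervals only for key feasibility proportions, and disclaims between-group and controlled pre-post inference. Tabulation by subgroup is often left to an analysis plan, and none is shown here. The timing flag exists, and using it would expose the selection. This stands in part. Pooling is the natural reading of section 2.10 but is not stated. What the article itself fixes is the entry condition, the outcome, the period covering pregnancy and postpartum, and a purpose for the flag that leaves out selection. The point concerns how those four combine.

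Three stronger readings are tempting, and the documents do not support them.

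- A reader might infer that the figure must rise with late entrants whatever the doula achieves. It does not rise if every prenatal entrant is suppressed in pregnancy, and a postpartum-only figure can stay flat or fall. If maintenance were counted only among women suppressed at entry, the gap would shrink; the article does not define that denominator.
- A reader might infer that only suppressed women can enter after delivery. The late-entry sentence suggests so, but the general criterion admits any postpartum woman, while sections 2.5 and 2.6 describe enrollment in pregnancy.
- A reader might infer that late entrants are at lower risk of losing suppression postpartum. That is plausible, but the article gives no data for it.

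It is also fair that the illustrated shifts lie well inside the interval for a sample of 15. Imprecision does not remove a dependence on recruitment mix, but it does limit what anyone should conclude from the figure.

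**Conclusion.** The point holds in a limited form. For women who enter under the late-entry sentence, the pregnancy part of an outcome listed as primary is met by definition and before the program begins, and section 2.10 does not separate them. A summary over both periods and all 15 women would rise with their number on two conditions: some prenatal entrants are unsuppressed during pregnancy, and postpartum maintenance is similar in the two groups.

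Under the illustrative rates (70% and 90%) the rise is 9 points for every five late entrants. It is 3 points if 90% of prenatal entrants are suppressed in pregnancy, and zero if all are. The rates and the number of late entrants are assumptions, so this shows a mechanism and is not an estimate of bias. The practical consequence is modest, because the study is a descriptive, exploratory pilot that frames clinical measures as signals. It is still worth correcting before enrollment, because the remedy is nearly free.

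**What to change.** **In 2.10:**
- Describe viral suppression separately by the prenatal/postnatal enrollment flag.
- For post-delivery entrants, count the postpartum period only, and label the group as selected for suppression at entry.
- Limit any overall figure to the postpartum period and show it beside the split.

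**In 2.4:**
- State that the flag is used for this selection as well as for differential exposure.
- Reconcile the late-entry sentence with the general criterion admitting pregnant or postpartum women, and with the statements in 2.5 and 2.6 that enrollment takes place in pregnancy. Which entry rule is intended is for the investigators to settle.

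**Cost:** a few sentences and one extra table column. The flag and the viral loads are already to be collected, so no new data are needed. The downside is smaller denominators and wider intervals, as the 7/10 and 12/15 intervals above show. The split also leaves one matter open: for prenatal entrants, suppression across pregnancy may include time before enrollment, so the text should say when each woman's observation starts.
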